#### Relevant interventions

2.4.4

##### Basic treatment in addition to the trial drug

2.4.4.1

Antiviral, antifibrosis, and liver protection therapies are allowed during the course (Table 2), but medications that directly affect blood ammonia or could improve cognitive performance (such as lactulose, lactitol, probiotics, and rifaximin) are prohibited until observable OHE.

**Table 2 T2:**
[figure not shown]
Basic treatments.

### Outcomes

2.5

The primary therapeutic outcome is the incidence measure of OHE within 24 weeks. An OHE attack is defined an adverse outcome.

The secondary outcomes are the results of the NCT-A, DST, SF-36, and CLDQ. The NCT-A and DST will be applied to measure patients’ neuropsychology performances, and an extended completion time will indicate cognition impairments.^[15,16]^ The SF-36^[17]^ and CLDQ^[18]^ are regular measurements of life quality among patients with hepatocirrhosis, and reduced scores for these tests designate impaired life quality.

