### Background

1.1

Minimal hepatic encephalopathy (MHE) is a unique disease stage of covert hepatic encephalopathy (CHE), and it is one of the complications caused by liver dysfunction.^[1]^ As it is in a subclinical state, it is difficult to identify, and it has no apparent psychologic or neurologic clinical manifestation. However, symptoms can be detected through sophisticated neuropsychologic and neurophysiologic tests.^[2]^ MHE debases patients’ quality of life by, for example, restricting their abilities to drive and work, and it is highly possible that MHE will further develop into overt hepatic encephalopathy (OHE).^[3]^ Therefore, MHE poses a significant potential hazard to individuals and society.^[4]^ Thus, it is significant to diagnose MHE and CHE and to prevent MHE from progressing to OHE. According to epidemiologic surveys, MHE or CHE occurs in 20% to 80% of patients with cirrhosiss.^[5–8]^ Therapies including lactulose, lactitol, probiotics, and rifaximin have been applied in the treatment and research of MHE, and they have shown the effect of preventing OHE from the first attack.^[9,10]^ However, none of these therapies is adequate for recommendation as a routine or preventive treatment. According to the 2014 Practice Guideline by the American Association for the Study of Liver Diseases, routine or preventive medicine is not recommended for MHE.^[11]^ The medical community lacks a clear consensus regarding how to treat the disease.

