### Trial design

1.3

We designed this trial as a double-blinded, randomized, and controlled exploratory trial. We will implement simple randomization with a 1:1 allocation ratio in 72 eligible patients. The primary endpoint is the occurrence of OHE within 24 weeks.

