### Statistical methods

4.3

We will carry out efficacy analyses with the full analysis set, which will include those who provided baseline data and at least one post-treatment assessment. Safety analyses will assess all of the randomly assigned patients.

We will apply a chi-square test to compare the occurrence of OHE attacks among groups.

We will assess the secondary outcomes with the Shapiro–Wilk test. We will assess the normally distributed data with *t* tests. We will assess data that were not normally distributed with nonparametric Wilcoxon rank-sum testing.

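### The primary endpoint counts OHE only, so on its literal text a death without OHE is scored like staying well or leaves the analysis; an OHE-or-death analysis should stand beside it

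*Protocol article*

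**What the plan says.** Four parts of the protocol article fix how the primary result is scored.

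- **Endpoint.** Section 1.3: "The primary endpoint is the occurrence of OHE within 24 weeks". Section 2.5 repeats it ("The primary therapeutic outcome is the incidence measure of OHE within 24 weeks") and adds: "An OHE attack is defined an adverse outcome". No other event is part of the endpoint, and death is not mentioned anywhere in the article.
- **Test.** Section 4.3: "We will apply a chi-square test to compare the occurrence of OHE attacks among groups". Whether a continuity correction applies is not stated.
- **Denominator.** Efficacy is analysed in the full analysis set, "which will include those who provided baseline data and at least one post-treatment assessment". Completing 24 weeks is not required. Visits are every 4 weeks (4.1).
- **Drugs that act on the endpoint.** Section 2.4.4.1 says that lactulose, lactitol, probiotics and rifaximin "are prohibited until observable OHE". Its stated ground is their effect on blood ammonia or cognitive performance. Separately, section 1.1 says of these therapies that "they have shown the effect of preventing OHE from the first attack". Rescue treatment is planned only after OHE (2.4.3.1).

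**The concern.** A patient who dies without OHE can no longer develop it. If OHE is the only event counted, that patient adds to the denominator and not to the numerator, and so lowers the OHE incidence of the arm. More such deaths under the formula would look like prevention. A death before the first post-treatment assessment does not lower the incidence in this way, but it is not counted against the arm either, because the patient leaves the analysis set.

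Use of a prohibited drug before OHE raises a related question. On the article's own account these drugs can prevent a first attack, and such a patient is likewise scored as OHE-free. The likely direction is not the same as for death. If the formula works, patients doing worse, and so more likely to be given such a drug, would be mainly controls. That would suppress control OHE and hide a real effect. Uptake mainly in the experimental arm would instead flatter the formula.

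**Working it through.** **The plan's own figure.** Section 2.7 sets 36 per group by choice, without a control rate, effect, alpha or power, so there is no calculation to reproduce. The weight of one patient is 1/36 = 2.8 percentage points.

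**Step 1: scoring on the literal text.**

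| Patient | In full analysis set? | Counted as OHE? |
|---|---|---|
| Well to week 24 | yes | no |
| Dies without OHE after the first assessment | yes | no |
| Dies before the first assessment | no | not analysed |
| Starts a prohibited drug before OHE, never has OHE | yes, once assessed | no |
| Develops OHE after the first assessment | yes | yes |

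The first, second and fourth rows get the same score.

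**Step 2: how few patients matter.** With a and b events in two arms of 36 and s = a + b, the uncorrected chi-square is 72(a − b)² / [s(72 − s)]. With continuity correction, (a − b)² becomes (|a − b| − 1)². All event counts are assumptions. Experimental arm first:

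| Table | Chi-square | p | p, corrected |
|---|---|---|---|
| OHE 4 v 11 | 72×49/855 = 4.126 | 0.042 | 0.082 |
| plus 1 experimental death, 5 v 11 | 72×36/896 = 2.893 | 0.089 | 0.156 |
| plus 2 experimental deaths, 6 v 11 | 72×25/935 = 1.925 | 0.165 | 0.267 |
| OHE 4 v 12 | 72×64/896 = 5.143 | 0.023 | 0.047 |
| plus 1 experimental death, 5 v 12 | 72×49/935 = 3.773 | 0.052 | 0.096 |
| plus 2 experimental deaths, 6 v 12 | 72×36/972 = 2.667 | 0.103 | 0.174 |

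For prohibited drugs in the other direction, OHE 5 v 10 gives 72×25/855 = 2.105, p = 0.147. Counting 3 treated controls as failures gives 5 v 13: 72×64/972 = 4.741, p = 0.030 (0.057 corrected).

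**Step 3: size of the bias in expectation.** Assume constant hazards and the same OHE hazard in both arms. Let r be the 24-week OHE risk without competing events and d the competing-event risk without OHE. With h = −ln(1 − r) and k = −ln(1 − d), the observed OHE risk is h/(h + k) × (1 − e^−(h + k)). For r = 0.30 and d = 0.05: h = 0.357, k = 0.051, risk 0.293. For d = 0.10: k = 0.105, risk 0.286. Summing exact binomial probabilities over all 36 v 36 tables gives the chance of a nominally significant result favouring the formula. Ranges are over r = 0.20 to 0.50, with control d = 5%:

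| Experimental d | Chance favouring the formula |
|---|---|
| 5% | 2.3–2.5–2.6% (equal risks, no bias) |
| 10% | 2.8–3.1% |
| 20% | 3.6–4.5% |
| 30% | 4.6–6.8% |

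**Step 4: prohibited drugs taken in the experimental arm only.** Let a share x take one, with an assumed OHE risk ratio rr. The experimental risk is 0.30 × [1 − x(1 − rr)] against 0.30 in controls. For x = 0.1 and rr = 0.6 it is 0.288; for x = 0.3 and rr = 0.4 it is 0.246. The chance of a significant result favouring the formula is 3.4% and 7.4% respectively.

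**The case against.** **Inference from silence.** A reader might infer that the plan declares these patients successes. No sentence says so, and an analysis plan or full protocol that is not shown may set a rule. This stands against that stronger reading. It does not remove the point: the article itself defines the endpoint as OHE alone and fixes the test and the analysis set, and the scoring follows from those three. An analysis plan that counted death as a primary failure would be changing the stated endpoint.

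**Early rescue passing for prevention.** A reader might infer this too. The documents do not support it as a planned pathway. Rescue follows OHE, so earlier use is a deviation of unknown frequency, and the plausible imbalance, if the formula works, hides an effect. Nor does 2.4.4.1 ban the drugs for preventing OHE; that remark is in 1.1.

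**Harm would be seen anyway.** Adverse events are documented at each visit, severe ones are reported to the committees (5.2), and safety covers all randomised patients (4.3). Deaths should therefore be known by arm. This stands, but it leaves the efficacy comparison unqualified.

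**The examples are selected.** They place all competing events in one arm, and 4 v 11 and 5 v 13 are not significant with continuity correction. That is right; 4 v 12 is the only starting table that stays below 0.05 either way. Patients with severe complications or malignancy are excluded (2.2.2), follow-up is 24 weeks and the trial is exploratory, so few deaths may occur and crossing 0.05 settles little.

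**Prohibited drugs as failure.** Counting OHE regardless of other drugs is a recognised strategy, and scoring a treatment decision as equal to OHE or death is a trade-off. This stands, and is why such use belongs in a sensitivity analysis.

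**Conclusion.** The point holds in a limited form. As fixed in 2.5 and 4.3, the primary comparison cannot distinguish a patient who died without OHE after the first assessment from one who stayed well, and it drops earlier deaths. Prohibited-drug use before OHE is also scored as no event.

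The bias requires an imbalance between arms. With competing-event risks of 10% versus 5%, the chance of a false result favouring the formula rises only from about 2.3–2.6% to 2.8–3.1%. It reaches 4.6–6.8% when the risks are 30% versus 5%. What makes the matter worth correcting is the small sample: at 2.8 points per patient, one or two deaths without OHE can decide nominal significance.

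These sizes rest on assumed OHE rates, competing risks, risk ratios and event counts, since the article gives none, and the power of the example tables to persuade depends partly on the uncorrected test.

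**What to change.** Keep OHE within 24 weeks as the primary endpoint. In 4.3, before unblinding, add:

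1. A prespecified supportive analysis of OHE or death from any cause within 24 weeks in all randomised patients. Show OHE, and deaths without OHE, by arm beside the primary result.
2. An interpretation rule: a lower OHE incidence is not presented as benefit if the OHE-or-death comparison does not support it. State in advance what counts as support. Agreement in direction alone is too weak: 4 v 11 and 6 v 11 agree in direction although the evidence has largely gone.
3. The number of patients per arm who started a drug prohibited by 2.4.4.1 before OHE, with a sensitivity analysis counting them as failures. Keep this out of the main composite.

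The cost is a few sentences, plus dates of death and of the first prohibited drug on the existing case report form, and OHE and vital status at week 24 for every randomised patient. The downside is that a composite mixes events of different clinical weight, so its components must always be shown.

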### Participant time line

2.6

The enrollment will begin in September and finish by approximately December 2018. The clinical observation will be completed by June 2019. The scheduled timeframe is displayed in Figure 1.

**Figure 1 F1:**
[figure not shown]
Scheduled intervention and assessments. CLDQ = chronic liver disease questionnaire, DST = digital sign test; laboratory tests include liver functions and blood ammonia, ECG = electrocardiogram, EEG = electroencephalogram, HBV serum markers, HBV DNA, blood routine tests, alpha-fetoprotein, NCT-A = number connection test A, PE = physical examinations, SF-36 = The Medical Outcomes Study item short-form health survey, 36 items.

### Sample size

2.7

Currently, the scientific community has inadequate information about the incidences of OHE that developed from MHE within a specified duration. In this pilot study, we set the sample size to 36 for each group, with 72 participants in total.

### Recruitment

2.8

Internal physicians will screen eligible patients from the clinic and inpatient department. The principal investigator will introduce the protocol as well as the benefits and risks of the study to the participants. An informed consent form is mandatory for enrollment.

## Method: assignment of interventions

3

### Allocation concealment

3.1

The ethics committee will generate a random number table (containing the patients’ IDs) using Microsoft Excel to settle the grouping plan; each group will be assigned 36 IDs, which will be in a disorganized sequence. Each eligible patient will be given a sealed envelope with an ID after enrollment.

### Blinding

3.2

The interviewers and patients will both be blinded to the grouping information of each participant. The trial drugs and placebos are consistent in color and taste. The ethics committee and data management committee will keep the allocation sequence and grouping information, which they will not release until final analysis or emergency unblinding.

## Method: data collection, management, and analysis

4

### Interviews

4.1

Patients will be interviewed every 4 weeks after enrollment in the clinic, where they should return the used packages and remaining drugs. Adequate trial drugs for 28 days will be dispatched during each interview. A series of tests will be conducted in different weeks (Fig. 1).

### Data management

4.2

Information obtained from each visit and the laboratory results will be recorded on printed case report forms. Electronic data will be manually inputted into double entries in electronic case report forms generated by EPIDATA software. Case report forms and data sets will be stored in the local archive center at Dongzhimen Hospital.

### Statistical methods

4.3

We will carry out efficacy analyses with the full analysis set, which will include those who provided baseline data and at least one post-treatment assessment. Safety analyses will assess all of the randomly assigned patients.

We will apply a chi-square test to compare the occurrence of OHE attacks among groups.

We will assess the secondary outcomes with the Shapiro–Wilk test. We will assess the normally distributed data with *t* tests. We will assess data that were not normally distributed with nonparametric Wilcoxon rank-sum testing.

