#### Trial drugs

2.4.1

Both groups will be treated with trial drugs for 24 weeks. The experimental group will receive 1 dose per day of the *JPHZXN* formula, whereas the control group will be given the *JPHZXN* formula placebo. The real drugs and placebos are consistent in shape, color, and taste.

The patients will be allowed to continue their basic treatment for hepatocirrhosis and CHB. In addition to receiving the trial drugs for MHE (Detailed in *2.4.4 Relevant interventions*).

The major ingredients of the *JPHZXN* formula are listed in Table 1.

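### The primary chi-square on 24-week OHE is run in a set that admits patients lost after one visit, who have no valid yes/no status; unequal losses then bias the comparison modestly, in a direction set by how they are counted

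*Protocol article*

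**What the plan says.** Three statements in the protocol article fix the primary analysis.

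- **Endpoint.** Trial design (1.3): "The primary endpoint is the occurrence of OHE within 24 weeks". Outcomes (2.5) agrees: "The primary therapeutic outcome is the incidence measure of OHE within 24 weeks". This is a cumulative incidence over a fixed window. The window equals the treatment period in Trial drugs (2.4.1): "Both groups will be treated with trial drugs for 24 weeks".
- **Analysis set.** Statistical methods (4.3) runs efficacy on "the full analysis set, which will include those who provided baseline data and at least one post-treatment assessment".
- **Test.** The same section: "We will apply a chi-square test to compare the occurrence of OHE attacks among groups". No event-time method is named.

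Other sections matter here. Interviews (4.1) sets clinic visits every 4 weeks, and Data management (4.2) has the information from each visit recorded on the CRF. Rescue medicine (2.4.3.1) has patients leave the cohort when OHE occurs; they have reached the endpoint, so this is not loss to follow-up. Sample size (2.7) gives 36 per group without a calculation and says that OHE incidence is poorly known. No dropout rate is given.

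**The concern.** The endpoint asks about 24 weeks, but membership of the analysis set asks for only one visit. If that visit is at week 4, a patient lost afterwards is in the set with up to 24 − 4 = 20 weeks unobserved. A chi-square test has no censoring. Each patient must be entered as an event, entered as a non-event, or left out.

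- **Entered as a non-event.** This is the literal result of comparing recorded OHE attacks in the stated set. Observed incidence falls in both arms, and falls more in the arm with more losses, which then looks better.
- **Left out.** Events are kept whenever they occurred, while non-events are kept only if followed to week 24. Observed incidence rises, and rises more in the arm with more losses, which then looks worse.

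So neither simple option repairs the test when losses are unequal, and the direction of the bias depends on which one is used. The primary result of a placebo-controlled trial would then partly reflect who stayed in it. Patients who die without OHE raise a similar question of status, because a yes/no table gives them no category of their own.

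**Working it through.** **The plan's own figure.** The plan states "we set the sample size to 36 for each group, with 72 participants in total", with no rates, alpha, power or effect behind it. There is nothing to reproduce.

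**Inputs from the article:** 36 per arm, a 24-week window, 4-weekly visits, and a set that needs one post-treatment assessment.

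**Assumptions:** two-sided 5% test; first post-treatment assessment at week 4; exponential OHE and dropout times; dropout unrelated to OHE risk; the same true 24-week risk p in both arms; dropout d by week 24 in the absence of OHE.

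**Formulas for each arm**

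- λ = −ln(1 − p)/24 and c = −ln(1 − d)/24
- OHE observed before loss: E = λ/(λ + c) × [1 − exp(−24(λ + c))]
- Lost before week 4, so outside the set: X = c/(λ + c) × [1 − exp(−4(λ + c))]
- Observed incidence, lost counted as event-free: E/(1 − X)
- Observed incidence, lost dropped: E/[E + exp(−24(λ + c))]

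**Worked case: p = 30%, dropout 10% v 40%.** λ = 0.01486; c = 0.00439 and 0.02128.

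- Low-dropout arm: E = 0.2856, X = 0.0169, so 0.2856/0.9831 = 29.1%
- High-dropout arm: E = 0.2385, X = 0.0793, so 0.2385/0.9207 = 25.9%
- False difference: 0.2905 − 0.2590 = 0.0315, or 3.2 points in favour of the arm with more losses. That is 0.0315 × 36 ≈ 1.1 patients.

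**Three null scenarios** (lower-dropout arm first)

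| True risk | Dropout | Lost = event-free | Difference | Lost dropped | Difference |
|---|---|---|---|---|---|
| 25% | 10% v 30% | 24.2% v 22.5% | +1.7 | 26.1% v 28.8% | −2.7 |
| 30% | 10% v 40% | 29.1% v 25.9% | +3.2 | 31.2% v 36.2% | −5.0 |
| 40% | 5% v 30% | 39.4% v 36.2% | +3.2 | 40.7% v 44.9% | −4.2 |

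**Type I error.** Simulations used at least 20,000 trials per scenario; the Monte Carlo standard error at 20,000 is √(0.05 × 0.95/20,000) ≈ 0.15 points. For the chi-square with lost = event-free, repeated runs gave 5.5% to 5.9%, 6.1% to 6.3% and 5.9% to 6.0% in the three rows. Log-rank with censoring gave 4.8% to 5.2%.

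**Beyond these rows.** At 40% risk with 10% v 40% dropout, the difference is 38.8% − 34.7% = 4.1 points and type I error is 6.9%. At the extreme of 0% v 50% dropout, type I error is 6.3% to 10.7% for risks of 20% to 50%. With equal dropout it stays near 5%.

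**When a true effect exists** (hazard ratio 0.5, control risk 40%). With dropout of 5% in control and 30% in the experimental arm, the chi-square with lost = event-free rejects in 43.5% of trials. With the losses reversed it rejects in 25.1%. If lost patients are dropped, the figures are 22.7% and 45.7%. Log-rank stays at 33% to 34%.

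**Price of changing the test.** For 30% v 8% OHE with 15% dropout in both arms, power is 65.2% for the chi-square and 65.1% for log-rank. At hazard ratio 0.5, 40% control risk and no dropout, it is 37.0% and 36.4%.

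**The case against.** A reader might infer that the plan counts lost patients and deaths as OHE-free and so manufactures a treatment effect. The article does not say that. It names a set and a test and is silent on how a lost or dead patient is classified. Patients with no post-treatment assessment fall outside the set, so they are not counted as event-free. Figures computed over all randomised patients (4.7 points in the worked case: 28.6% v 23.8%) therefore overstate the bias in the planned set.

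Three further objections are fair.

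- **The missing-data rule may sit in a full protocol or SAP.** Its absence from a condensed article is not an error. This stands, but the point does not rest on it: the article itself fixes a set and a test that do not fit the endpoint unless follow-up is complete. The two simple completions both bias the result when losses are unequal.
- **A chi-square suits a fixed-window binary endpoint.** This also stands. With complete follow-up it is valid, and ignoring event times costs almost no power here.
- **Log-rank assumes non-informative censoring.** This stands too. If patients leave for reasons linked to their OHE risk, censoring does not fully remove the bias.

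The trial is also described as an exploratory pilot, which limits the weight of a small excess in type I error. Its primary objective is still whether the formula lowers OHE occurrence, so the 24-week incidence in each arm is its main product.

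**Conclusion.** The point holds in a limited form. The stated set and test leave patients lost between the first visit and week 24 without a valid yes/no status, and unequal losses bias the comparison whichever simple rule is applied.

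Under the literal reading, the false difference is about 2 to 3 points and type I error about 6% in the three null scenarios, against about 5% for log-rank. Stronger imbalance at higher risk gives more. All of these sizes rest on assumed OHE and dropout rates and on non-informative dropout. With equal dropout, type I error is held and the two tests have the same power; with complete follow-up there is no problem. The change is worth making because it costs almost nothing, not because the bias is shown to be large.

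**What to change.** In Statistical methods (4.3):

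- Make the primary analysis time from randomisation to first OHE within 24 weeks, in all randomised patients, censored at last contact.
- Test with log-rank, using a permutation p-value because events will be few. Report the Kaplan-Meier 24-week incidence in each arm and their difference with a 95% CI.
- Treat death or transplant without OHE as a competing event, and in that case estimate incidence by Aalen-Johansen.
- Keep the chi-square as supportive, with its rule for lost patients stated. Add a sensitivity analysis for dropout related to OHE risk.

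The cost is wording in 4.3 and making sure that the OHE date and last-contact date are on the CRF. The CRF is not shown, so they may already be there; with 4-weekly visits, onset is known at least to the visit interval. The remaining limitation is that the primary estimate assumes non-informative censoring, which is why the sensitivity analysis is needed.

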#### Secondary objectives

1.2.2

The secondary objectives are to determine whether the *JPHZXN* formula could improve the performance in number connection test A (NCT-A) and the digital sign test (DST) as well as the quality of life of patients with MHE (evaluated by the Medical Outcomes Study item short-form health survey—36 items [SF-36] and chronic liver disease questionnaire [CLDQ]).

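### Secondary outcomes: a Shapiro-Wilk test on the trial's own data selects an unadjusted t or Wilcoxon test, so the effect measure is data-driven and precision is lost against a pre-fixed baseline-adjusted analysis

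*Protocol article*

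**What the plan says.** The Outcomes section (2.5) lists the secondary endpoints: "The secondary outcomes are the results of the NCT-A, DST, SF-36, and CLDQ". The secondary objectives (1.2.2) are framed as change for the better: "formula could improve the performance in number connection test A (NCT-A) and the digital sign test (DST"). Quality of life is put in the same terms.

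Statistical methods (4.3) sets the analysis in three steps:

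- Every secondary outcome first goes through a normality check: "We will assess the secondary outcomes with the Shapiro–Wilk test".
- Scales that pass it are compared between arms by *t* test.
- For the remaining scales the plan is: "We will assess data that were not normally distributed with nonparametric Wilcoxon rank-sum testing".

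No covariate, model or effect measure is named, and the text does not say whether the tests apply to final scores or to change from baseline. The same section admits a patient to the full analysis set only with baseline data and at least one assessment after treatment starts.

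On size, section 2.7 says "we set the sample size to 36 for each group, with 72 participants in total". It gives no power calculation, because "the scientific community has inadequate information about the incidences of OHE that developed from MHE within a specified duration". Section 2.4.3.1 adds that patients who progress to OHE leave the trial cohort.

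**The concern.** There are two separate weaknesses.

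The first is the selection step. A t test compares means and a rank-sum test compares ranks. If a normality test on the trial's own data chooses between them, the quantity reported for each scale is unknown until the data are seen, and the four scales can end with different effect measures. For a trial that calls itself exploratory and a pilot, the useful product is an estimate with an interval that a later trial can be planned on. This procedure does not reliably deliver one.

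The second is efficiency. Cognitive test times and quality-of-life scores usually correlate with their own baseline values. A two-sample test on final scores leaves that variation in the error term. A test on change scores removes it only in part, and adds noise when the correlation is below 0.5. With 36 patients per arm, precision is scarce.

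**Working it through.** **Inputs from the article.** 36 per arm, 72 in total (2.7), allocated 1:1 (1.3). The article gives no SD, effect size, correlation or alpha, and its sample size is not derived, so there is no stated figure to reproduce.

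**Assumptions.** Two-sided alpha 0.05; true effect 0.5 SD; baseline-to-follow-up correlation r from 0.3 to 0.7; equal variance at baseline and follow-up; a score from all 72 patients.

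**Variance relative to an unadjusted final-score comparison.**

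- Final score: 1
- Change score: 2(1 − r)
- ANCOVA: 1 − r²
- ANCOVA relative to change score: (1 − r²) / [2(1 − r)] = (1 + r)/2

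**Power (normal approximation).** Power = Φ(0.5 / (s·√(2/36)) − 1.96), where s is the square root of the variance factor and √(2/36) = 0.236. For the final-score test, 0.5/0.236 = 2.12 and 2.12 − 1.96 = 0.16, giving 56.4%. A calculation with the t distribution gives 55.3%.

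| r | ANCOVA variance factor | Cut vs final score | Cut vs change score | Equivalent total N, 72/(1 − r²) | Power, change score | Power, ANCOVA |
|---|---|---|---|---|---|---|
| 0.3 | 0.91 | 9% | 35% | 79 | 43.4% | 60.4% |
| 0.5 | 0.75 | 25% | 25% | 96 | 56.4% | 68.8% |
| 0.6 | 0.64 | 36% | 20% | 113 | 66.0% | 75.5% |
| 0.7 | 0.51 | 49% | 15% | 141 | 78.2% | 84.4% |

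The equivalent N is relative to the final-score test. The difference detectable with 80% power is 0.66 SD for that test. Under ANCOVA it falls to 0.63, 0.57, 0.53 and 0.47 SD for the four correlations.

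**The selection step.** The two-stage procedure was simulated with 10,000 runs and 36 per arm. Shapiro-Wilk was applied in each arm at 5%, and the Wilcoxon test was used if either arm failed. The article specifies neither the level nor whether arms are tested separately, so both are assumptions.

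| Data | Quantity | Two-stage | t alone | Wilcoxon alone | Sent to Wilcoxon |
|---|---|---|---|---|---|
| Normal, no effect | Type I error | 0.050 | 0.049 | 0.046 | 10% |
| Lognormal (σ = 0.5), no effect | Type I error | 0.052 | 0.048 | 0.051 | 96% |
| Normal, 0.5 SD effect | Power | 0.553 | 0.553 | 0.526 | 10% |

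The simulation standard error for a rate near 0.05 is √(0.05 × 0.95 / 10,000) = 0.002, so neither two-stage error rate differs materially from 5%. About one truly normal outcome in ten still changes its effect measure by chance. Power with skewed data was not simulated.

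**The case against.** The strongest reply is that this is a condensed article, that an analysis plan may exist, and that covariates and model form are commonly left to it. Silence about a covariate would indeed be no finding. But section 4.3 is not silent: it names the tests and the rule for choosing between them. That is a stated method, and it can be compared with a better one.

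Several stronger readings are tempting, and the article does not support them.

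- **That the plan ignores baseline altogether.** The variable tested is not named, and an objective of improvement would fit change scores. What stands is that no baseline term is stated and that ANCOVA is more precise under either reading for the correlations considered, apart from one degree of freedom.
- **That all four scales are certainly measured at baseline.** This is a strong inference from the full analysis set rule and the neuropsychology tests required at entry. The schedule in Figure 1 is not shown, so the readable text does not confirm it.
- **That most of the information is wasted.** The gain depends on a correlation the article does not give. At r = 0.3 it is only 9% against final scores.
- **That the p-values are invalid because of the pre-test.** The simulation shows no material inflation, and no power loss with normal data. The fault lies in the effect measure.
- **That chance baseline imbalance biases the comparison.** Under randomization the unadjusted comparison is unbiased and its standard error already covers such imbalance. The cost is precision.

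It is also fair to object that an ANCOVA restricted to week 24 could drop patients who leave the cohort at OHE, and that such exits would lower every power figure above. The first part shapes the fix; the second is a limit on the figures.

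**Conclusion.** The point holds as one of efficiency and prespecification, of moderate weight. As stated, section 4.3 lets the data choose the effect measure for each secondary scale and uses no baseline term. For correlations of 0.3 to 0.7, ANCOVA reduces variance by 9% to 49% if final scores are tested and by 35% to 15% if change scores are tested. For a 0.5 SD effect, power goes from about 55% with a final-score t test to between about 60% and 84%. Against a change-score test the contrast runs from 43% versus 60% at r = 0.3 to 78% versus 84% at r = 0.7.

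These sizes rest on assumed correlations, an assumed effect, complete data in 36 per arm, and baseline measurement of each scale. A reader should not infer an error-rate problem or any consequence for the primary comparison of OHE occurrence. Only secondary outcomes of a pilot trial are affected.

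**What to change.** In section 4.3, replace the Shapiro-Wilk, t and Wilcoxon sequence with one analysis per scale, fixed before unblinding, that adjusts for the baseline score and reports the adjusted difference between arms with a 95% CI. Two forms would serve:

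- ANCOVA of the final score on treatment and baseline score.
- A baseline-adjusted repeated-measures model using all scores after treatment starts. This suits the trial better if the scales are measured at several visits, because patients with OHE leave the cohort and the analysis set requires only one such assessment. An ANCOVA on week-24 scores alone would drop patients who have none.

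Any transformation of NCT-A time should be fixed in advance. The section should also say how scores missing after OHE are handled, and confirm that each scale is taken at baseline.

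The cost is one degree of freedom and slightly more analysis work. If the baseline scores are collected, no new data or patients are needed, and the primary chi-square analysis stays as it is.
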